### Assignment of interventions: allocation

#### Sequence generation

In accordance with central randomization and a completely randomized grouping method, 240 three-digit random numbers were generated by SPSS statistical software. Subsequently, each three-digit number was recorded as a random number corresponding to a patient. The patients were numbered from 001 to 240 in the order of admission, corresponding to the random numbers. Then, the 240 random numbers were sorted from smallest to largest. (The data were consistent when numbered sequentially.) It was stipulated that patients with serial numbers 001 to 120 belonged to the acupuncture group, and those with serial numbers 121 to 240 were in the control group.

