### Sample size

Regarding the design of the sample size calculation formula, we referred to the 8th edition of "Epidemiology" published by the People's Health Publishing House [27]. The formula is presented as follows: *N* = 2(Z₁₋α/₂ + Zβ)²σ²/d². In this formula, Z₁₋α/₂ represents the value corresponding to the first type of error probability, and Zβ denotes the value for the second type of error probability. σ is the standard deviation estimated through literature study [[17], [18], [19], [20], [21], [22], [23], [24], [25]], with σ=0.80 kg/m². d is the difference between the means of the two groups as estimated through literature study [[17], [18], [19], [20], [21], [22], [23], [24], [25]]. The mean value was 6.76 kg/m² in the acupuncture group and 6.08 kg/m² in the sham acupuncture group, thus *d* = 0.68 kg/m². Substituting the above data into the formula yields a sample size of 36 cases per group. Considering a 10 % dropout rate, the number of cases to be included in each group should be no <40. Since a 1:1 ratio is employed for both groups, 80 cases are needed at each center, totaling 240 cases.

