### Statistical methods

#### Statistical methods for primary and secondary outcomes

The main efficacy indicators will be analyzed using both the full analysis set (FAS) and per protocol set (PPS). The other efficacy indicators will be analyzed via the FAS set, while the safety indicators will be analyzed with the safety set (SS). The baseline equilibrium analysis will also be carried out using the FAS set.

Statistical analysis encompasses statistical description and statistical inference. For the statistical description of quantitative indicators, it includes mean, standard deviation, median, minimum value, and maximum value. Qualitative indicators are depicted by frequency tables and constituent ratios. Statistical inference involves interval estimation and hypothesis testing. For quantitative indicators, their two-sided 95 % confidence intervals (CIs) will be estimated. Each efficacy indicator will undergo bilateral testing with a significance level of α = 5 %. The null hypothesis posits that there is no statistically significant difference between the test group and the control group, whereas the alternative hypothesis contends that there is a statistically significant difference between the two groups. When *p* < 0.05, the null hypothesis will be rejected, and the difference between the two groups is deemed statistically significant.

Regarding measurement data, normality analysis is performed first. All data conforming to normal distribution are expressed as mean ± standard deviation. For comparison within the same group before and after treatment, the paired *t*-test is utilized, and for comparison between groups, the independent samples *t*-test is employed. For non-normally distributed measurement data, the rank sum test is adopted. For non-graded data in count data, the chi-square or non-parametric test is used. For graded data, the Ridit test is applied. In a bilateral test, a P value <0.05 is considered as a statistically significant difference.

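### The allocation rule does not say which serial number sets the arm, one unstratified list does not deliver the implied 1:1 split at each centre, and allocation is marked before some baseline measurements

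*Protocol article*

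**What the plan says.** **Rule for the arm (Protocol article, Sequence generation).** The method is described as central and completely randomised, using 240 three-digit random numbers from SPSS. "The patients were numbered from 001 to 240 in the order of admission" and paired with the random numbers, which are then sorted in ascending order. A bracketed remark about sequential numbering follows, and then the rule: "It was stipulated that patients with serial numbers 001 to 120 belonged to the acupuncture group, and those with serial numbers 121 to 240" are controls. No centre stratification or blocking is mentioned. Concealment mechanism and Implementation add that codes are withheld until a patient is enrolled, that a program generates a 1:1 sequence, and that an independent researcher assigns patients.

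**Numbers per centre (Sample size).** The formula gives 36 per group. After allowing for a 10% "dropout rate, the number of cases to be included in each group should be no <40". The section then concludes, from the 1:1 ratio, that "80 cases are needed at each center", 240 in total.

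**Timing (Participant timeline).** Allocation is marked in the -t1 column, defined as recruitment and diagnostic screening. QCT, circumferences, irisin/myostatin, blood tests and ECG are first marked at 0, defined as baseline. ASM, handgrip strength, walking speed, FTSST and SPPB are marked at -t1, the same column as allocation.

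**Related text.** Assignment of interventions: Blinding leaves subjects and researchers unblinded and gives result evaluation to investigators unaware of the grouping. The retention section gives each subject one fixed researcher for treatment and all examinations. The planned between-group comparison of normally distributed measurements is an independent-samples t-test with no term for centre.

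**The concern.** Three linked points about how patients reach their arms.

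1. The term serial number is used without saying whether it means the admission number or the position after sorting. One meaning gives a random allocation. The other gives a predictable one that is fully confounded with calendar time. A reader of the published method cannot tell from the wording alone which was used.
2. A per-centre target at 1:1 is paired with a list that does not enforce it. Needling depends on the operator, and blood samples are handled under local protocols at each centre. A chance difference in centre mix between arms therefore adds variation that the stated t-test does not remove.
3. Where subjects and staff are unblinded, a baseline taken after allocation can be coloured by knowledge of the arm. Here that concerns secondary and safety measures.

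**Working it through.** **Step 1: reproduce the plan's sample size.** Inputs from Sample size: "with σ=0.80 kg/m²" and d = 6.76 − 6.08 = 0.68 kg/m². Two-sided α = 0.05 comes from the statistical methods. The power is not stated.

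N per group = 2(Z₁₋α/₂ + Zβ)²σ²/d², with σ²/d² = 0.64/0.4624 = 1.384.

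| Assumed power | N per group |
|---|---|
| 80% | 22 |
| 90% | 30 |
| 95% | 2 × (1.960 + 1.645)² × 1.384 = 35.97, so 36 |

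Of these, only 95% power reproduces the 36. Then 36/0.90 = 40 per group, 40 × 2 = 80 per centre, and 80 × 3 = 240. The 1:1 ratio within 80 per centre implies 40 per arm per centre, although the protocol does not write it in those words.

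**Step 2: the two readings of the rule.**

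- *Admission number:* admissions 1 to 120 all receive acupuncture and 121 to 240 all receive sham. The random numbers and the sort then play no part.
- *Rank of the random number:* a valid random 120:120 allocation, consistent with the sort and with a concealed, computer-generated sequence.

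The rank reading needs a rule for ties. If 240 three-digit numbers are drawn with replacement, the chance of no tie is the product of (M − i)/M for i = 0 to 239. This is 2.6 × 10⁻¹⁴ for M = 1000 values and 5.5 × 10⁻¹⁶ for M = 900. Ties are practically certain unless the draw was without replacement, and the protocol does not say which was done.

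**Step 3: centre balance under the rank reading.** Assume exactly 80 patients per centre. The acupuncture count in one centre is hypergeometric (240 in total, 120 acupuncture, 80 drawn).

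- Variance = 80 × 0.5 × 0.5 × (160/239) = 13.39, so SD = 3.66; central 95% range 33 to 47.
- P(a given centre is 40:40) = 0.109.
- P(all three are 40:40) = C(80,40)³/C(240,120) = 0.0137.
- P(a given centre has 36 to 44 on acupuncture) = 0.782, so P(an arm below 36 in that centre) = 0.218.
- P(at least one of the three centres has an arm below 36) = 0.43, from 100,000 random permutations.

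**Step 4: what the imbalance costs.** At 33:47, efficiency within that centre relative to 40:40 is 4 × 33 × 47/80² = 6204/6400 = 0.97, a loss of about 3%. On the plan's own d and σ, power is 0.950 at 36 per arm and above 0.9999 at 108 per arm (120 less 10%). The pooled comparison is not at risk.

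**Step 5: order of allocation and baseline.**

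| Measure | First marked | Relative to allocation (-t1) |
|---|---|---|
| QCT, circumferences, irisin/myostatin, blood tests, ECG | 0 | after |
| ASM, handgrip, walking speed, FTSST, SPPB | -t1 | order not fixed |

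The documents give no interval between -t1 and 0 and nothing from which to size an effect on the time-0 measures.

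**The case against.** The strongest reply is that the design is sound and only the wording is loose. Drawing and sorting random numbers serves no purpose unless serial number means rank, and codes are said to be withheld until enrolment. That largely stands. A reader might infer that the first 120 admitted are in fact given acupuncture and that staff can foresee the next arm. The documents do not support this: it is one literal reading, and the surrounding text points the other way. What remains is that the published rule does not say so and is silent on ties.

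On centres, unstratified randomisation is a legitimate choice, no within-centre test is planned, and the list fixes 120 per arm. This also stands. A reader might take the 43% figure as a loss of power or as bias. It is neither: the 36 is already met by the whole trial several times over, and chance imbalance under random allocation does not bias the estimate in expectation.

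On timing, the table has merged headings, and the Enrolment heading appears to span both -t1 and 0, with the post-allocation period starting at t1. The trial design section also places the first recordings before treatment. QCT and laboratory values are less open to assessor influence, and evaluators are said to be unaware of the grouping. These points soften the concern. They do not remove the mark for allocation at -t1 or the arrangement in which one fixed researcher handles both treatment and examinations. A reader might infer that the primary outcomes are measured after allocation; the table does not show that.

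**Conclusion.** The point holds in a limited form, in three parts.

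- **Rule.** Sequence generation is ambiguous. The rank of the random number is the likely meaning, but the text should say so, because its only explicit patient numbering would make the allocation non-random.
- **Centre.** The single list does not deliver the implied 40:40 at each centre. The consequence is modest noise that the stated unadjusted t-test leaves in place, not a threat to the pooled 120 per arm. The probabilities assume exactly 80 patients per centre and the rank reading.
- **Timing.** As the timeline is laid out, allocation precedes the baseline for QCT, circumferences, irisin/myostatin and the safety tests. For ASM, handgrip and the function tests the order is unspecified. This rests on the column positions in the timeline table, and the size of any effect cannot be derived from the documents.

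Together these merit correction while recruitment is under way, as Protocol validation says it is. They do not show that the trial has been allocated wrongly.

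**What to change.** 1. State in Sequence generation that the rank of the random number, not the admission number, sets the arm. Give the rule for ties, and confirm that this was the rule actually used. Cost: a few sentences and a check of the existing list.
2. Place allocation at time 0, after all baseline measurements are complete, and move its mark in the Participant timeline to match. Cost: a protocol amendment and a change in visit order for patients still to enrol.
3. Replace the unadjusted between-group t-test with an analysis that includes centre as a covariate, for all patients. Cost: a change to the analysis text only; N stays 240.
4. Optional: centre-stratified permuted blocks for patients still to enrol. Do this only if the new lists account for those already allocated, so that the 120:120 total is kept, and if the date of the change is recorded. The cost is a change of method during recruitment; item 3 secures most of the benefit without it. Stratification by sex is not needed for this point.

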#### Concealment mechanism

The computerized randomization program will not release the random codes until the patients are enrolled in the study, thus ensuring allocation concealment. Due to the differences in the operational methods between acupuncture and sham acupuncture, it is impossible to blind the researchers. However, the data collection and analysis will be completed by professional statisticians. The subjects and researchers will be unaware of the data, while the statisticians will be unaware of the study groups.

#### Implementation

The principal investigators at each center will recruit subjects. A computerized randomization program will generate an allocation sequence at a ratio of 1:1. An independent researcher will assign the participants to the acupuncture group and the sham acupuncture group.

### Assignment of interventions: Blinding

Due to the characteristics of the intervention study, in the design of the acupuncture intervention, blinding will not be applied to the subjects and researchers regarding the intervention measures. However, the data analysts will be blinded to the allocation of the intervention measures. The result evaluation and statistical analysis will be conducted by independent investigators who are unaware of the patient grouping.

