## Abstract

Sarcopenia (SP) is an age-related disorder characterized by progressive loss of muscle strength, mass, and limb dysfunction, severely compromising the quality of life and life safety in older adults. With the global aging population, the incidence of this disease has been escalating, posing a significant public health challenge. Preclinical studies have demonstrated that acupuncture effectively mitigates muscle loss in rats; however, the field currently lacks robust randomized controlled trials (RCTs), marked by limitations such as the absence of sham acupuncture controls, multicenter designs, and standardized outcome metrics. Therefore, this study integrates acupuncture with exercise therapy, incorporating the following design highlights:

A multicenter approach to enhance research reliability;

A control group receiving sham acupuncture combined with exercise to eliminate the placebo effect;

The most comprehensive and validated set of outcome measures to ensure study rigor and expand the conceptual framework for sarcopenia assessment.

This research aims to provide robust evidence for acupuncture as an effective adjuvant therapy for SP. The study has been registered with the International Traditional Medicine Clinical Trials Registry Platform (ITMCTR2024000374).

AbbreviationsSPSarcopeniaRCTsRandomized Controlled TrialsASMAppendicular Skeletal Muscle MassSMISkeletal Muscle IndexDXAdual-energy X-ray absorptiometryQCTQuantitative Computed TomographyFTSSTFive-Times-Sit-to-Stand TestSPPBShort Physical Performance BatteryIGF-1Insulin-like Growth Factor-1TNF-αTumor Necrosis Factor-αIL-6Interleukin-6SODSuperoxide DismutaseGSH-PxGlutathione PeroxidaseCRCClinical Study CoordinatorECGElectrocardiogramFASFull Analysis SetPPSPer Protocol SetSSSafety SetITTIntention-To-TreatDMCData Monitoring CommitteeIECEthics Committee

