**Value of the Protocol**	1. SP severely compromises quality of life and survival in older adults, with its incidence escalating alongside global aging. However, mainstream treatments for SP are associated with limitations: exercise therapy alone suffers from low adherence, nutritional support carries the risk of exacerbating renal burden, and hormone therapy exhibits significant side effects. Thus, there is an urgent need to explore effective adjunctive and alternative therapies for SP. 2. Previous clinical studies on acupuncture for SP have been plagued by flaws such as the absence of multicenter designs and lack of sham controls. Therefore, this study will employ a multicenter RCT to enhance reliability, complemented by a sham acupuncture control group to minimize the placebo effect. 3. Previous research in this field has suffered from inconsistent and incomplete efficacy endpoints. Thus, this study introduces a comprehensive set of primary and secondary endpoints, encompassing muscle strength, muscle mass, physical function, and muscle-related serum biomarkers.

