### Interventions

#### Explanation for the choice of comparators

Exercise therapy is currently the main treatment approach for SP. From the perspectives of traditional Chinese medicine theory and modern medical research, acupuncture has the efficacy of promoting muscle growth. Then, will combining acupuncture with other mainstream therapies for SP further enhance the curative effect? Does acupuncture treatment for SP have a placebo effect? What are the specific mechanisms by which acupuncture improves SP? How effective is acupuncture specifically in terms of indicators such as muscle strength, muscle mass, and muscle function? We still lack strong clinical evidence in these aspects. Therefore, we have designed sham acupuncture combined with exercise therapy as the control group.

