#### Sham acupuncture group treatment protocol

In this group, the combination of sham acupuncture [32,33] and exercise therapy will be adopted. Sham acupuncture is performed by superficially pricking with a 0.30 mm × 40 mm needle at a location 2 cm away from the lateral edge of each acupoint selected for the acupuncture group (non-meridian and non-acupoint sites). No needle manipulation is involved, and the needle is retained for 30 min.

The exercise therapy in this group is identical to that in the acupuncture group. Similarly, the treatment and follow-up schedules are the same as those of the acupuncture group.

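### The blinding section says patients are not blinded, contradicting the placebo claims for the sham arm and leaving handgrip and the performance tests without control of patient expectation

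*Protocol article*

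**What the plan says.** On masking, the section Assignment of interventions: Blinding states that "blinding will not be applied to the subjects and researchers regarding the intervention measures". It adds a protection on the assessment side: "The result evaluation and statistical analysis will be conducted by independent investigators who are unaware of the patient grouping".

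The section Concealment mechanism is narrower: "Due to the differences in the operational methods between acupuncture and sham acupuncture, it is impossible to blind the researchers". That sentence is about researchers. The same section says subjects are kept from the data; it does not say they are kept from their allocation.

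On the purpose of the sham arm, the Abstract lists as a design highlight "A control group receiving sham acupuncture combined with exercise to eliminate the placebo effect". The Specifications table, under Value of the Protocol, says the multicenter design is "complemented by a sham acupuncture control group to minimize the placebo effect". Explanation for the choice of comparators asks "Does acupuncture treatment for SP have a placebo effect" and gives that gap in evidence as a reason for the sham control.

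On the sham itself, the Sham acupuncture group treatment protocol begins "Sham acupuncture is performed by superficially pricking with a 0.30 mm". It specifies a needle of the same size as in the active arm, placed beside each selected point, without manipulation, and retained for the same 30 minutes.

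**The concern.** A sham procedure isolates the specific effect of needling because both arms hold the same beliefs about what they receive. If patients know their arm, that equality is lost and the contrast between arms mixes needling with expectation. The protocol sets out this advantage over earlier trials, which it criticises for lacking sham controls, and then states that the condition it depends on will not be met.

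What is at stake differs by outcome. Handgrip is a maximal voluntary contraction and a primary outcome. Walking speed, FTSST and SPPB are also performed by the patient. On these, a patient who believes the treatment is real may simply try harder. Blinding the person who reads the dynamometer does not remove that.

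**Working it through.** **1. Do the sections agree on patient masking?**

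| Section | Patients | Researchers | Evaluators and analysts |
|---|---|---|---|
| Blinding | not blinded | not blinded | blinded |
| Concealment mechanism | unaware of the data; allocation not mentioned | cannot be blinded | statisticians blinded to group |
| Sham procedure | not mentioned, but needle size and retention time match the active arm | – | – |
| Abstract, Value of the Protocol, choice of comparators | placebo control claimed, which presupposes masking | – | – |

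Only the Blinding section makes a direct statement about patients, and it says they are not blinded. The reason given under Concealment mechanism, different operating methods, covers the operator only. The Blinding section offers just a general reference to the nature of the intervention. Neither explains why a patient could not be masked to this sham.

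**2. Does blinded evaluation fill the gap?** It would limit assessor bias but not patient expectation. It is also in doubt: the section on participant retention assigns each subject a fixed researcher who is responsible for both treatment and all examinations.

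**3. Which outcomes are exposed?**
- *Directly:* handgrip (primary), 6-meter walking speed, FTSST, SPPB.
- *Indirectly:* ASM by DXA (primary), L3 muscle area and density by QCT, serum irisin and myostatin. Expectation can reach these only through exercise effort, whose intensity is raised individually, or through dropout that differs by arm.

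**4. The protocol's sample size, for scale.** Inputs from the section Sample size: SD 0.80 and difference 0.68 kg/m²; two-sided α = 0.05 from Statistical methods. The power is not stated.

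n = 2(z₁₋α/₂ + z_power)² σ²/d² = 2(1.960 + 1.645)² × 0.64/0.4624 = 35.97, so 36 per group.

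The stated 36 is reproduced at 95% power, which is therefore inferred; 80% gives 22 and 90% gives 30. With 10% dropout, 36/0.9 = 40. The trial enrols 240, that is 120 per arm, or 120 × 0.9 = 108 evaluable.

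**5. What could an expectation shift do? (Illustration on assumed values.)** Suppose needling has no specific effect and knowledge of the arm shifts an effort-dependent outcome by δ SD. The test statistic is then centred at t = δ√(108/2) = 7.348δ, and the two-sided rejection rate is 1 − Φ(1.96 − t) + Φ(−1.96 − t).

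| Assumed δ (SD) | t | Rejection rate |
|---|---|---|
| 0 | 0 | 5% |
| 0.1 | 0.73 | 11% |
| 0.2 | 1.47 | 31% |
| 0.3 | 2.20 | 60% |
| 0.5 | 3.67 | 96% |

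A larger sample raises these rates, so sample size is no protection. The documents give no value for δ; the table shows sensitivity and is not evidence that a bias exists.

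**The case against.** The strongest reply is that the sentence is a drafting slip. The concealment section limits the impossibility of blinding to researchers, and a sham with the same needle size and retention time makes little sense if the arm is disclosed. No section says patients are told their arm. This stands as a caution: a reader might infer that patients have in fact been told, and the documents do not support that. It does not remove the defect, because the only direct statement on patient masking says there is none, and the article describes itself as the complete protocol.

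A second reply concerns scope. A reader might infer that the trial cannot separate acupuncture from placebo on any outcome. The documents do not support that either. ASM, QCT and serum markers are not voluntary-effort measures, the exercises are supervised, and result evaluation is stated to be blinded. The indirect routes remain possible but unquantified.

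A third concerns dropout. Withdrawal for dissatisfaction with efficacy is open to both arms and covers exercise as well as acupuncture. With 120 per arm enrolled against 36 needed, exceeding the 10% allowance would not by itself threaten the stated power. What remains is possible bias if dropout differs by arm. The protocol already names attrition bias as a limitation, but not in relation to knowledge of allocation.

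Finally, an article may leave the details of keeping and checking masking to the full protocol. That is fair. The point here is a statement that contradicts the design's purpose, not missing detail.

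**Conclusion.** The contradiction is real and must be corrected. Followed as written, the plan leaves one of two primary outcomes (handgrip) and three secondary outcomes (walking speed, FTSST, SPPB) without control of patient expectation, while the article claims that control as a main advance. For ASM by DXA, QCT and the serum markers the exposure is indirect and its size unknown.

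The conclusion rests on reading the blinding section literally. If patients are in practice masked, the fault lies in the text and the trial's placebo control may be intact. If they are not, the placebo claims cannot stand for the effort-dependent outcomes. The rejection rates of 11% to 96% depend on assumed shifts of 0.1 to 0.5 SD and carry no weight beyond illustration.

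**What to change.** **First, establish the facts.** The section Protocol validation says recruitment and treatment are under way and outcome assessment has not been reached. Find out from the consent form and the sites what enrolled patients have been told, then reconcile Concealment mechanism, Blinding and the sham treatment protocol. At the same time, reconcile blinded evaluation with the retention section's single researcher for treatment and examinations.

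**If patients are or can be masked,** amend the Blinding section, for example: *Patients are blinded to real versus sham needling until their last visit. Acupuncturists are not blinded. Outcome evaluators and data analysts are blinded.* Match the consent wording. Ask each patient one allocation-guess question at day 60 and report the answers by arm. Flag any patients already told their arm and give a sensitivity analysis without them.

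**If patients are not masked,** withdraw the placebo claims in the Abstract and in Value of the Protocol, describe the comparison as open-label for patients, and interpret handgrip and the performance tests accordingly.

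**Cost.** Masking needs an ethics amendment, consent wording and one question at an existing visit; the sham is already delivered. If some patients were already told, the cohort becomes a mix of masked and unmasked patients. The sensitivity analysis could then lose many of those enrolled so far, and it would no longer compare fully randomised groups if disclosure differed by arm. Withdrawing the claim costs only text, but gives up a main stated advantage of the design.
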